### Flow of study subjects

Figure 2 describes the study subject’s flow, and the subsequent parts of this protocol outline each step in detail.

**Fig. 2 Fig2:**
[figure not shown]
Flow of study subjects

### Recruitment

At each study site, pharmacist will actively identify patients who meet the eligibility criteria. Participants will be provided a detailed explanation regarding the purpose and procedures of the trial. Patients who express their agreement to participate will be required to provide a written informed consent before enrolment. For patients with neurological or psychiatric illnesses, the consent and signature of their caregivers or legal representatives will also be obtained.

Participants will be recruited if they meet the following inclusion criteria: (1) patients aged ≥ 60 years old; (2) taking more than five regular drugs at the time of admission; (3) taking at least one chronic medical condition using International Classification of Diseases, Tenth Revision, Clinical Modification (ICD-10-CM); (4) can understand and speak Malay, English, or Mandarin language.

Patients will be excluded if they: (1) are admitted for end-of-life care; (2) diagnosed with terminal illness; (3) diagnosed with active cancer; (4) participated in another drug trial; (5) refused or unable to give consent; (5) visited the Emergency Department without admission to ward; (6) readmitted and have been previously enrolled in the trial.

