### Randomization

A stratified-cluster randomization design will be adopted for this trial, with the 14 hospitals serving as the unit of randomization. This design was chosen specifically to address the potential "contamination" effect that may arise among individuals within the same ward. The cluster design effectively controls for the potential "contamination" effect that may arise among individuals (pharmacists, doctors, patients) within the same ward, where changes in one individual's behaviour may have the potential to influence others. Furthermore, this approach offers the advantage of significant time savings compared to individual randomization. The principal investigator performed the randomization.

Given that larger and smaller hospitals may have different administrative capacities, it was crucial to ensure a balanced distribution of patients across both intervention and control arms. To achieve this, trial sites were stratified and clustered based on the number of yearly admissions in each hospital as follows:i.Hospitals with 4001–5000 yearly admissions (total of 5 hospitals; intervention: 3; control: 2)ii.Hospitals with 3001–4000 yearly admissions (total of 6 hospitals; intervention: 3; control: 3)iii.Hospitals with 1500–3000 yearly admissions (total of 3 hospitals; intervention: 1; control: 2).

This approach ensures a balanced and comparable distribution of patients in both the intervention and control groups.

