### Blinding

Blinding is not possible due to the nature of the intervention. As such, participants assigned to the intervention group will be informed regarding the intervention. In the control group, all participants, physicians, and ward pharmacists will continue to receive and provide their usual care without any knowledge of the intervention. Routine pharmacist medication review services will address significant drug errors identified, which will be communicated to the physicians.

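### Patients are identified and consented after their hospital is allocated, with unequal knowledge of the intervention by arm and no stated safeguard against differential selection

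*Protocol article*

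**What the plan says.** All places are in the Protocol article.

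- **Randomization.** The design is a stratified cluster randomisation "with the 14 hospitals serving as the unit of randomization". Allocation is reported as done: "The principal investigator performed the randomization". Hospitals are stratified by yearly admissions, and the section concludes: "This approach ensures a balanced and comparable distribution of patients in both the intervention and control groups".
- **Recruitment.** Patient selection is still to come: "At each study site, pharmacist will actively identify patients who meet the eligibility criteria". On information and consent: "Participants will be provided a detailed explanation regarding the purpose and procedures of the trial", and "Patients who express their agreement to participate will be required to provide a written informed consent before enrolment". Eligibility rests on age, number of regular drugs, a chronic condition and language, plus a list of exclusions. Having a PIM is not a criterion.
- **Overview of trial design** and **Intervention arm.** Ward pharmacists lead the deprescribing and receive half a day of training on it. MALPIP review is the first step of the intervention.
- **Blinding.** The trial is open label, and "participants assigned to the intervention group will be informed regarding the intervention". Control patients, physicians and ward pharmacists "will continue to receive and provide their usual care without any knowledge of the intervention".
- **Sample size calculation.** The number of patients per site is set according to yearly admissions.

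**The concern.** Randomising hospitals makes the hospitals comparable on average. It does not make the enrolled patients comparable if they are approached and asked for consent once the arm is fixed and recruiters or patients know different things in the two arms. A pharmacist trained to look for inappropriate drugs may notice or favour different patients from one who has heard nothing of the intervention. Patients told about deprescribing may accept or refuse for reasons that do not arise in the other arm.

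At stake is the baseline case mix: PIM and medication count at admission, frailty, and hence the risk of falls, emergency visits, readmission and death. A difference there would be mixed with the effect of the intervention. Admission PIM, medication count and EQ-5D-5L are measured, so imbalance in those could be seen and adjusted for. Unmeasured differences, such as willingness to stop drugs, could not.

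**Working it through.** **1. Order of events.** Randomization reports allocation in the past tense; Recruitment describes identification and consent in the future tense. With hospitals as the unit, every patient is therefore approached at a site whose arm is already set. Nothing in the text places identification or consent before allocation. The flow figure is not shown, so the order is inferred from tense and design.

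**2. Who knows what, by arm.**

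| | Intervention hospitals | Control hospitals |
|---|---|---|
| Ward pharmacists | Trained in the intervention and lead it | No knowledge of it (Blinding) |
| Patients | Informed of it (Blinding) | No knowledge of it (Blinding), yet given the trial's purpose and procedures (Recruitment) |
| Recruiter | A pharmacist at the site | A pharmacist at the site |

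The first row shows unequal knowledge among the professional group that recruits. The second row holds the conflict: an account of the purpose and procedures of a deprescribing trial cannot easily leave control patients knowing nothing of the intervention.

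**3. What the stated design features control.** Stratification by yearly admissions balances hospital size. Clustering limits contamination within a ward. Neither governs which patients are approached or agree after allocation. The independent t-tests planned for emergency visits and hospitalisations (Data analysis) carry no adjustment for case mix.

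**4. Room for selection.** The strata under Randomization imply total yearly admissions between

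- 5 × 4001 + 6 × 3001 + 3 × 1500 = 42,511, and
- 5 × 5000 + 6 × 4000 + 3 × 3000 = 58,000.

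The target is 500 patients, or 500/14 ≈ 36 per hospital, which is 500/58,000 ≈ 0.9% to 500/42,511 ≈ 1.2% of one year's admissions. Not all admissions are eligible and the recruitment period is not stated, so this shows only that there may be ample choice.

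**5. Scale, as an illustration.** Inputs from Sample size calculation: SD 0.39, difference 0.13, two-sided alpha 0.05, power 90%. The plan's own figure first:

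n per arm = 2 × [0.39 × (1.960 + 1.282) / 0.13]² ≈ 189.1, against the stated 189.

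Now suppose no true effect, and a difference d in mean PIM that comes from selection alone. With independent patients, SE = 0.39 × √(2/n), which is 0.0401 for n = 189 and 0.0349 for n = 250. The chance of a significant result is Φ(−1.96 + d/SE) + Φ(−1.96 − d/SE).

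| Assumed d (PIM) | Share of 0.13 | n = 189 per arm | n = 250 per arm |
|---|---|---|---|
| 0 | 0% | 5% | 5% |
| 0.02 | 15% | 8% | 9% |
| 0.039 | 30% | 16% | 20% |
| 0.065 | 50% | 37% | 46% |
| 0.078 | 60% | 49% | 61% |

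Every d is an assumption. The formula is symmetric in sign, so it says nothing about which arm would look better. It ignores clustering; a larger standard error that allowed for clustering would lower the percentages in the last two columns but leave the shares of 0.13 unchanged.

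**The case against.** The article is a condensed account. Screening order, logs and information sheets often sit in a full protocol, and the flow figure is not available. The text says that pharmacists identify patients who meet the criteria, not that they pick among them. This has force: silence on sampling order would not be a finding by itself. What remains is that the procedure as stated, followed to the letter, lets selection and consent differ by arm.

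Several stronger readings are tempting, and the documents do not support them.

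- *All recruiters know their arm.* A reader might infer this from the open label. It is clear only for trained ward pharmacists in intervention hospitals; Blinding says that control ward pharmacists have no knowledge of the intervention. Nor does Recruitment say that the recruiter is the person who delivers the intervention. The supported point is unequal knowledge.
- *MALPIP is used to choose patients.* PIM is not an eligibility criterion, MALPIP review is part of the intervention, and consent comes before enrolment.
- *The two arms have different consent texts.* Recruitment describes one explanation for all. The sentence under Blinding does not mention consent and may refer to the later discussion with the patient. What the text shows is a conflict, not an established difference in documents.
- *Selection would favour the intervention.* Enrolling patients with more PIMs in that arm would tend to raise its PIM at discharge and so work against it in the discharge comparison that sizes the trial. Regression to the mean could inflate an analysis of change. The direction is open.

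The sentence about comparable patients under Randomization can also be read as concerning patient numbers rather than case mix. On that reading it is not wrong, but it offers no protection here either.

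**Conclusion.** The concern stands as a risk. Allocation precedes recruitment, knowledge of the intervention is unequal between arms, and no stated feature of the design prevents differential selection or consent. Case mix could therefore differ and bias PIM, medication count and the clinical outcomes. It does not follow that every outcome is biased: the documents give no size or direction, and the percentages above rest on assumed shifts and independent patients.

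The conclusion depends on the inferred order of allocation and recruitment, and on no safeguard being set out elsewhere. The conflict between Recruitment and Blinding over what control patients are told depends on neither and must be reconciled in any case. The point should be addressed; it does not call for a change to the allocation or the sample size.

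**What to change.** 1. At all 14 hospitals, take consecutive admissions from the ward list on set recruitment days. Approach eligible patients in list order, using only the criteria under Recruitment, until the site's number is reached.
2. Keep a short screening log (eligible, approached, consented) and report it by arm.
3. Reconcile Recruitment with Blinding, so that what patients are told before consent is as alike as possible in both arms. This involves a trade-off: fuller information for control patients may bring back some of the contamination that the cluster design was meant to avoid. The sponsor should weigh the two and state the choice.

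The cost is slightly slower recruitment, less convenience for pharmacists, a simple log and possibly an ethics amendment.

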### Control arm

All participating patients will receive the standard routine care typically provided at each respective site. This includes preadmission medication reconciliation and medication review routinely conducted by the pharmacists. Adherence to routine practices in the control arm is integral to ensuring comprehensive patient care and align with the standard procedures implemented within the healthcare setting.

### Intervention arm

In the intervention group, a four-step deprescribing process will be employed, whereby: i) pharmacist review using MALPIP criteria to detect PIM on all the admission and discharge medications; ii) discussion with doctors for deprescribing decisions; iii) discussion with patients and documentation of shared decisions; iv) follow-up patients (Fig. 3).

**Fig. 3 Fig3:**
[figure not shown]
Four-step pharmacist-led deprescribing framework

Pharmacists will conduct deprescribing interventions and engage in discussions with doctors during daily medical ward rounds, where deprescribing decisions will be made based on the pharmacists' suggestions and the attending doctors' judgment. Following this, the pharmacists will communicate the deprescribing proposals to patients, and document the decision whether it was approved or rejected by the physicians. Patient outcomes, including medication usage, quality of life, falls, and readmission rates, will be assessed throughout the study. The complete MALPIP list can be found at https://sites.google.com/moh.gov.my/malpip/home and the mobile application can be downloaded from Google Play Store: https://play.google.com/store/apps/details?id=pack.geridea.

To ensure standardization, pharmacist serving each of the medical ward will receive a half-day face-to-face training session on the intervention. To ensure data integrity, the principal investigator will perform data validation by reviewing a randomly selected 20% of the study data, focusing on the accuracy of PIM coding.

### Blinding

Blinding is not possible due to the nature of the intervention. As such, participants assigned to the intervention group will be informed regarding the intervention. In the control group, all participants, physicians, and ward pharmacists will continue to receive and provide their usual care without any knowledge of the intervention. Routine pharmacist medication review services will address significant drug errors identified, which will be communicated to the physicians.

### Measurements

Table 1 describes the outcomes that will be measured in this trial. Falls will be classified using ICD-10 codes based on patient-reported data. The number of emergency department visits and readmissions to hospitals will be based on hospital medical records and patients' reported data. Survival status at 6, 12 and 18 months will be retrieved from the National Registration Department database at the end of the trial.

Chronic medications will include drugs prescribed consistently for more than 28 days prior to the assessment day (Bayliss et al. 2020), excluding certain medication categories such as toxoids, vaccines, local anaesthetics-parenteral, antiseptics and disinfectants, and antidotes, as per the 2-digit GPI codes classification.

To assess the subject's quality of life, the Malaysian-validated version of EQ-5D-5L will be employed [26], which offers greater robustness compared to EQ-5D-3L [27, 28]. The face-to-face and telephone interview versions of the questionnaire are obtained from the EuroQoL office, and they are available in Malay, Chinese, and English languages. The choice of administration will be based on the subject's preference.

### Data analysis

All analyses will adhere to the intention-to-treat principle, complemented by per-protocol analysis as sensitivity analyses. Descriptive statistics will be employed to analyse the baseline characteristics of the patients. The change in the mean number of chronic medications and potentially inappropriate medications (PIM) across four time-points will be assessed using repeated measures ANOVA. Independent t-tests will be utilized to compare the number of emergency department (ED) visits and hospitalizations between the control and intervention groups. A p-value of less than 0.05 will be deemed statistically significant. IBM SPSS Statistics for Windows version 24 (IBM Corporation, NY, USA) will be employed for statistical analyses.

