### Outcome measures

The primary outcome of the trial is the total number of chronic medications and PIM taken by older adults at five time-points (admission, discharge, 6 months, 12 months and 18 months post-randomization).

The secondary outcomes include fall events, number of emergency department visits, number of ADE-related and all-cause readmissions to the hospital, and mortality at 6 months, 12 months, and 18 months post-randomization. The total number of pharmacists' interventions and acceptance by doctors will be measured at discharge. The quality of life will be measured at admission, discharge, 6 months, 12 months, and 18 months post-randomization (Table 1).

**Table 1 Tab1:** Primary and secondary outcomes, instruments, and time-points

	Instruments	Time-points
Primary outcome		
1. PIM	MALPIP	Admission, discharge, 6 months, 12 months and 18 months
2. Chronic medications	Medication prescribed continuously for more than 28 days prior to the assessment day	Admission, discharge, 6 months, 12 months and 18 months
Secondary outcome		
1. Recommendations made by pharmacists and accepted by physicians	Pharmacists’ pharmacotherapy review form and patients’ case note	Discharge
2. Fall event	Medical records and self-reported using ICD-10 codes	discharge, 6 months, 12 months and 18 months
3. Emergency Department (ED) visit	Medical records and self-reported	6 months, 12 months and 18 months
4. ADE-related and all-cause readmissions	Medical records and self-reported	6 months, 12 months and 18 months
5. Quality of life	EQ-5D-5L	Admission, discharge, 6 months, 12 months and 18 months
6. Survival status	National Registration Department database	discharge, 6 months, 12 months and 18 months

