### Sample size calculation

Sample size was calculated based on the primary outcome: the reduction in the mean number of PIM in discharge. According to Wehling et al. [24], the mean number of PIMs at discharge for the intervention group was 0.15, while the mean number of PIMs at discharge for the control group was 0.28 [24]. For an alpha risk of 0.05 and a 90% power, standard deviation 0.39, it was estimated that 189 patients would be needed per arm (378 patients in total) to detect a 0.13 reduction in the mean number of PIM [24]. Projecting a subject dropout rate of 25%, the total number of subjects required will be 500, or 250 per arm. The number of samples per trial site will be stratified based on yearly admissions. Sample size was calculated using Power and Sample size online calculator, compare two proportions, two-sample, two-sided equality test [25].

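### Repeated measures ANOVA and t-tests on raw counts fit poorly with intention-to-treat when 25% dropout and deaths are expected: unless values are imputed, the first keeps only completers, and the second ignores time at risk

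*Protocol article*

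**What the plan says.** The Data analysis section sets the principle: "All analyses will adhere to the intention-to-treat principle, complemented by per-protocol analysis as sensitivity analyses". It then names the methods. The change in mean number of chronic medications and PIM "across four time-points will be assessed using repeated measures ANOVA". For the utilisation outcomes, "Independent t-tests will be utilized to compare the number of emergency department (ED) visits and hospitalizations between the control and intervention groups". The software is "IBM SPSS Statistics for Windows version 24".

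The Outcome measures section collects the primary outcomes "at five time-points (admission, discharge, 6 months, 12 months and 18 months post-randomization".

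The Sample size calculation rests on mean PIM at discharge (0.28 vs 0.15), with these inputs: "For an alpha risk of 0.05 and a 90% power, standard deviation 0.39". It arrives at 189 per arm and adds: "Projecting a subject dropout rate of 25%, the total number of subjects required will be 500, or 250 per arm".

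Death is a secondary outcome. The Measurements section takes survival status at 6, 12 and 18 months from the national registration database, and the abstract's hypothesis includes lower mortality with the intervention.

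**The concern.** Classical repeated measures ANOVA needs a complete row of visits for each patient. Someone who is lost or dies at month 10 has a discharge value and a 6-month value, but both leave the analysis because the later visits are absent. The result describes patients who survived and completed 18 months. That is not the population promised by the intention-to-treat statement, and in an open-label trial loss can differ between arms.

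The t-tests compare numbers of events with no denominator. A patient who dies early has less time in which to visit an ED or be readmitted, so the comparison mixes the event rate with survival. If the intervention lowers mortality, as the trial hypothesises, the raw counts are tilted against it. If mortality went the other way, they would be tilted in its favour. The Discussion names readmission and mortality among the evidence gaps that the trial is meant to fill.

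**Working it through.** **Inputs from the protocol article.** Difference 0.13, SD 0.39, two-sided alpha 0.05, power 90%, 189 per arm, 25% dropout, 500 enrolled (Sample size calculation); follow-up to 18 months (Outcome measures). No mortality rate, event rate or rate of missed visits is given, so every such figure below is an assumption.

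**1. The plan's own figure.** n per arm = 2 × [0.39 × (1.960 + 1.282) / 0.13]² = 189.1, against 189 stated. With dropout, 378 / 0.75 = 504, against 500 stated. The sample size is reproduced closely by the two-means formula.

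**2. Patients excluded by a complete-case ANOVA.** Taking the 25% as patients without 18-month data, 0.25 × 500 = 125 are excluded and 375 remain. If a further 5% or 10% also miss each of two other visits (assumed), 500 × 0.75 × 0.95² = 338 or 500 × 0.75 × 0.90² = 304 remain. So 125 is not an upper limit.

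**3. Nominal power at discharge.** Power = Φ(0.13 / (0.39 × √(2/n)) − 1.96), which treats patients as independent and compares the two arms at discharge only.

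| n per arm | Power |
|---|---|
| 250 (all discharge values used) | 96.1% |
| 189 (planned completers) | 90.0% |
| 187.5 (250 less 25%) | 89.8% |

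The loss from 96% to 90% was planned for. The remaining issue is which patients are analysed.

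**4. Time at risk and raw counts.** With deaths spread evenly over follow-up, mean time at risk as a fraction of 18 months is 1 − mortality/2. Assume the same event rate while alive in both arms.

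- 20% vs 15% mortality: 0.900 / 0.925 = 0.973, so 2.7% fewer events in the arm with more deaths.
- 25% vs 15%: 0.875 / 0.925 = 0.946, so 5.4% fewer.

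Constant hazards give nearly the same answer: at 25% vs 15%, mean time at risk is 1.304 vs 1.384 years, a ratio of 0.942. A wider assumed gap of 30% vs 20% gives 1.262 / 1.344 = 0.94.

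**5. What a rate leaves unsolved.** A simulation was run in which frailer patients both die and have events more often (gamma frailty with variance 1, one event per person-year, mortality 20% vs 30%, no true effect on events; all assumed). Raw mean counts were 1.20 vs 1.05. Rates per person-year were still 0.90 vs 0.84. A time-at-risk denominator removes part of the distortion, not all of it. In the same simulation, with PIM number also tied to frailty and no true effect on it, mean PIM among 18-month survivors was 0.224 vs 0.196, against 0.28 in everyone. This is selection on the level of PIM; it does not by itself show bias in change.

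**The case against.** **Listwise deletion is not written in the article.** This is correct. It is how the named method behaves when a visit is missing, and imputation beforehand would keep the patients. An analysis plan that is not shown might specify that. A reader might infer that the intention-to-treat claim is already broken; the documents support only the conditional statement. What stands is that the method itself is fixed in the text, sits poorly with the stated principle, and has a better alternative.

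**Power is not short.** Also correct. A reader might take 96% vs 90% as a deficit, but 90% is the planned power and 500 were to be enrolled to absorb the loss. Inflation does nothing about who the completers are.

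**Harm passing for benefit.** A reader might go this far, but it needs more deaths in the intervention arm together with equal event rates while alive. The article gives no mortality rate, and the shifts at the smaller assumed gaps are about 3% to 5%, not shown to reverse a conclusion. If harm also raised admissions before death, counts could rise. Mortality is reported as an outcome, so an excess would be visible. Hospital records also supply ED visits and readmissions, so a patient who stops contact does not necessarily stop being observed. These limit the size of the problem; the missing denominator remains.

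**Skewed counts.** With about 250 per arm this is a weak argument against a t-test, and the point does not depend on it.

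**Four versus five time-points.** A reader might conclude that one visit has been dropped. Change from admission gives exactly four: discharge, 6, 12 and 18 months. This is a wording ambiguity, though it matters because the modelled visits decide who is excluded.

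**Conclusion.** The point holds in conditional form and should be corrected before analysis. Unless missing values are imputed, the named ANOVA turns the primary analysis into one of completers, leaving out about 125 of 500 patients at the projected dropout and discarding discharge values already observed. This rests on 25% being the share without complete visits. The bias in the PIM comparison cannot be sized from the document.

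The t-tests on counts confound event rate with survival whenever mortality differs between arms, a difference that the trial's own hypothesis expects. The size is about 3% at 20% vs 15% mortality and about 5% at 25% vs 15%, under assumed mortality, evenly spread deaths and equal event rates while alive. The direction depends on which arm has more deaths; if the intervention lowers mortality, it works against the intervention.

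**What to change.** **PIM and chronic medications.** Use a mixed model on every observed visit at discharge, 6, 12 and 18 months, with the admission value as covariate, a hospital random effect and a small-sample correction for 14 clusters. Keep all patients by their hospital's allocation. Such a model implicitly extends trajectories beyond death, so state that these results are interpreted among those alive.

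**ED visits and readmissions.** Use negative binomial regression with log time at risk as offset and a hospital effect. The article promises survival status at 6, 12 and 18 months, not death dates. Request the date of death in the same registry query or, failing that, approximate time at risk from the three status checks.

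**Death and dropout.** Report deaths beside each result and add a sensitivity analysis for informative death and dropout, since neither the mixed model nor the offset fully resolves them.

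**Visits.** State in the Data analysis section that the four time-points are the post-admission visits, to agree with the five measured in the Outcome measures section.

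The cost is revised analysis wording, modest extra programming and possibly one more field in the registry request. Recruitment, intervention and visit schedule stay as they are.

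### The 90% power is for the between-arm difference in PIM count at discharge, but the planned analysis tests change over four unnamed time-points without the admission count as a covariate

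*Protocol article*

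**What the plan says.** Three sections of the protocol article describe the primary PIM outcome.

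- **Outcome measures** defines a count at each visit: "The primary outcome of the trial is the total number of chronic medications and PIM taken by older adults at five time-points". The five are admission, discharge and 6, 12 and 18 months. Table 1 schedules PIM and chronic medications at all five.
- **Sample size calculation** uses one visit: "Sample size was calculated based on the primary outcome: the reduction in the mean number of PIM in discharge". Its inputs are two arm means, "the mean number of PIMs at discharge for the intervention group was 0.15" and "the mean number of PIMs at discharge for the control group was 0.28", with the remaining settings given as "For an alpha risk of 0.05 and a 90% power, standard deviation 0.39". It gives no admission mean, admission SD or correlation between visits.
- **Data analysis** states: "The change in the mean number of chronic medications and potentially inappropriate medications (PIM) across four time-points will be assessed using repeated measures ANOVA". It does not say which four time-points, whether the arm effect or the arm-by-time effect decides, or that the admission count enters as a covariate.

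**The concern.** The trial is sized on a level at one visit and analysed as movement over several. These have different standard errors, so a power figure calculated for one does not carry over to the other.

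They also respond differently to a chance difference between arms at admission. Only 14 hospitals are randomised, seven per arm, so such a difference is plausible. In the same data, the discharge comparison and the change comparison could then give different effect sizes, or fall on different sides of the significance threshold. The trial is open-label, and the text does not fix which of the two answers is the primary one.

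**Working it through.** **1. Reproduce the plan's figure.** Inputs from the Sample size calculation section: difference 0.28 − 0.15 = 0.13, SD 0.39, two-sided alpha 0.05, power 90%.

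n per arm = 2 × [0.39 × (1.960 + 1.282) / 0.13]² = 189.1, against 189 stated. Power at 189 per arm: SE = 0.39 × √(2/189) = 0.0401; Φ(0.13/0.0401 − 1.96) = 90.0%.

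That section names a two-proportions calculator, but 0.28 v 0.15 as proportions needs 208 per arm (205 with unpooled variance). The stated figure is thus a comparison of two means at one visit, with no baseline term.

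**2. Power for the other candidate quantities.** Keep 189 per arm and 0.13. Two things are assumed: the admission-discharge correlation ρ, over a range, and an admission SD of 0.39. Clustering is set aside to isolate this point.

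- Level at discharge: SD = 0.39
- Change from admission: SD = 0.39 × √(2(1 − ρ))
- Discharge adjusted for admission: SD = 0.39 × √(1 − ρ²)

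Power = Φ(0.13 / (SD × √(2/189)) − 1.96).

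| ρ | Level | Change | Adjusted |
|---|---|---|---|
| 0 | 90% | 63% | 90% |
| 0.3 | 90% | 78% | 92% |
| 0.5 | 90% | 90% | 96% |
| 0.7 | 90% | 99% | 99.5% |

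Example at ρ = 0.3: change SD = 0.39 × √1.4 = 0.461, SE = 0.0475, Φ(2.74 − 1.96) = 78%.

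The adjusted column is never below the others, because 1 − ρ² ≤ 1 and 1 − ρ² = (1 − ρ)(1 + ρ) ≤ 2(1 − ρ). It does not depend on the admission SD. The change column does: an admission SD above 0.39 would lower it.

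**3. If admission is not among the four time-points.** Suppose they are discharge, 6, 12 and 18 months, and the 0.13 difference is sustained. The arm-by-time effect is then zero, so that test has power equal to alpha (5%). The arm effect averaged over those four visits, with equal correlation ρ between visits, has power 98% at ρ = 0.5 and 96% at 0.7. Here too the stated 90% is not the power of the test.

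**4. Size of a chance imbalance at admission.** With 250 per arm, 250/7 = 35.7 patients per hospital, SD 0.39 and an assumed intracluster correlation (ICC) of 0 to 0.05:

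SE = 0.39 × √(2 × (1 + 34.7 × ICC) / 250) = 0.035 to 0.058 PIM, which is 27% to 44% of 0.13.

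**5. Effect of an imbalance on the estimates.** Take a true effect of −0.130, the intervention arm 0.05 higher at admission, and ρ = 0.5.

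| Source of imbalance | Level | Change | Adjusted (patient level) |
|---|---|---|---|
| Between patients, regressing with ρ | −0.130 + 0.025 = −0.105 | −0.130 − 0.025 = −0.155 | −0.130 |
| Hospital difference persisting to discharge | −0.130 + 0.050 = −0.080 | −0.130 | −0.080 − 0.025 = −0.105 |

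Level and change differ by the full 0.05 in both rows. Which of them is off, and by how much, depends on where the imbalance comes from.

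**The case against.** Several objections have force.

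- **No change score is defined.** Repeated measures ANOVA takes the count at each visit as its dependent variable, and the wording can mean how visit means move over time. That stands. The change column in the working is conditional on one reading. It does not rescue the 90%, because step 3 shows that the figure does not carry over to the main alternative reading either.
- **A covariate can be left to the analysis plan.** That stands: its absence from a condensed article would not be a finding. The point rests on the printed mismatch between the sized and the analysed quantity.
- **The arm-by-time term may already use baseline.** If admission is one of the four time-points, it does so by differencing. That is not covariate adjustment, and the text does not say that admission is included.
- **Adjustment is not a complete cure.** That stands: with a persistent hospital difference, patient-level adjustment removes only part of the error, and change is the unbiased comparison.

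A reader might infer that the trial is underpowered for its analysis. The documents do not support this: change has less power than stated below ρ = 0.5 and more above it, and ρ is not given. A reader might also infer that one of the comparisons is biased. Under randomisation both have the same expected value, and they part only through realised imbalance. Calling the 0.13 a reduction is not a substantive error either, since both arm means are printed beside it.

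**Conclusion.** The mismatch is in the text and should be resolved. The 189 per arm and 90% power describe a between-arm difference in mean PIM count at discharge; the planned ANOVA tests something else. For change from admission, power at the same size runs from about 63% (ρ = 0) to 99% (ρ = 0.7). Adjustment for the admission count gives 90% to 99.5% over the same range and is never worse than either alternative under these assumptions.

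The figures rest on an assumed ρ, on an admission SD of 0.39 for the change column, and on clustering being set aside. The direction of the power discrepancy is unknown. The size and direction of any error from admission imbalance depend on whether the imbalance is between patients or a persistent hospital difference. This is an improvement in analysis wording that needs no new data, not evidence that the design fails.

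**What to change.** - In Outcome measures, Sample size calculation and Data analysis, define one primary comparison: the between-arm difference in PIM count (and in chronic medication count) at the post-admission visits.
- Replace the ANOVA of change with a model for those visits that has the patient's admission count as a covariate, not as an outcome visit, and that accounts for hospital. Where imbalance lies between hospitals, the hospital mean admission count can also be considered, at the cost of a degree of freedom among 14 clusters.
- In Sample size calculation, state that the 0.13 and the 90% power refer to the between-arm difference in mean PIM at discharge.
- Keep change from admission as a descriptive summary.

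The cost is wording and model specification only. Table 1 already schedules the admission counts, so no patients, visits or data items are added.
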